#### Hypotheses

To examine the mechanisms through which TRE leads to symptom improvements, we will investigate a battery of biological measures at baseline and 8 weeks. We predict that TRE adherence will lead to a change in the amplitudes of diurnal clock gene expression and diurnal phase (DLMO) at 8 weeks, which will lead to a cascade of change in symptoms (mania and depression at week 10, and then a downstream change in QOL at 16 weeks).

H1: TRE adherence will predict changes in diurnal amplitude of clock gene expression from baseline to week 8.H2: The degree of change in diurnal amplitude of clock gene expression (at week 8) will be associated with the degree of improvement in symptoms (week 10), controlling for change in glucose tolerance and inflammation (week 8) and for baseline levels of diurnal amplitude, symptoms, glucose tolerance, and inflammation.H3: There will be an indirect effect of TRE adherence on QoL through symptoms.

Ambulatory data will provide opportunity for lagged tests of how biological rhythmicity improvements (actigraphy RA) promote improved sleep, resulting in diminished mood variability (ecological momentary assessment; EMA Mood Zoom) [74].

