#### Primary outcomes

Our primary outcome measures will be: interview-based assessments of mood symptoms, and a brief self-report measure of Quality of Life, which were chosen based on strong psychometric characteristics, including high interrater reliability for the interview-based measures. Where possible, the symptom severity interviews will be conducted by raters who are unaware of the participant’s intervention status (which is feasible as our team is conducting a parallel study involving the Mediterranean diet). Where a rater becomes inadvertently aware of the intervention status, we will attempt to replace the interviewer for that participant.

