### Statistical analysis plan

Before conducting analyses of hypotheses, we will examine whether values appear to be missing at random. If this missing value imputation assumption is supported, we will impute data using 20 resamples, using demographic (sex/gender, age), baseline symptom severity, and symptom history variables (number of episodes) to predict missing scores. For comparison, we will perform analyses without imputed values. Data cleaning will be completed as described above in data quality. Statistical analyses will be conducted in accordance with the International Conference on Harmonization E9 statistical principles.

Before conducting analyses of hypotheses, we will carefully examine potential confounds. We will avoid adding any covariates that were entangled with our core mechanisms (e.g., sleep and circadian processes). With this in mind, we will only consider covariates for inclusion in models if they could be confounding our main effects– that is, those that are significantly correlated with both our IV (treatment adherence) and DVs (symptoms and QoL). Power analyses were based on inclusion of two covariates, and we would hope not to exceed this number of covariates. If more than two potential covariates are identified that appear significantly and uniquely correlated with both the IV and DVs, we would redo our power analyses, but at this point, we would be able to consider the covariance matrices, allowing for more careful estimation of true statistical power. We would consider these issues without generating the models of how our treatment variables actually influence symptoms and QoL, so as to avoid p-hacking or “fishing”. Only if those power analyses suggested that we could include more than 2 variables as confounds would we proceed to add more covariates; otherwise, we would plan to choose the two covariates that appear to hold the highest unique correlations with IV and DVs.

Analyses will be conducted using two-tailed tests with alpha set to .05.

Our core hypotheses will be tested using two parallel structural equation models (SEM) to consider mania and depression separately. In each, we will examine paths from TRE adherence levels to a latent variable for clock gene amplitude (based on 3 genes) to symptoms to QoL, controlling expected covariates and evaluating the potential confound of glucose tolerance mediation.

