We have planned analyses based on availability of data from 125 participants, allowing for attrition of 25 participants. We assume moderate effects for diurnal amplitude on symptoms and QoL (f2 = .25) because smaller effects are inconsistent with the circadian rhythm theory. Assuming f2 = .40 (symptoms to QoL), power to detect the indirect effect of change in amplitude of gene expression on QoL via symptom change is .81, and for full model (RMSEA) > .90 [130, 131]. Intervention-related effects will be estimated using an intention-to-treat approach, in which we will examine final scores (where available) for all participants.

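### Mania and depression are tested in two separate SEMs at .05, with no rule for combining them and no term for the other symptom in either

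*Protocol article*

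**What the plan says.** The Statistical analysis plan section of the protocol article sets the error level: "Analyses will be conducted using two-tailed tests with alpha set to .05". It then fixes the structure: "Our core hypotheses will be tested using two parallel structural equation models (SEM) to consider mania and depression separately". In each model, "we will examine paths from TRE adherence levels to a latent variable for clock gene amplitude (based on 3 genes) to symptoms to QoL".

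Under Primary outcomes, "Our primary outcome measures will be: interview-based assessments of mood symptoms, and a brief self-report measure of Quality of Life". Table 1 lists these as MADRS, YMRS and QoL.BD.

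Under Hypotheses, H3 reads: "There will be an indirect effect of TRE adherence on QoL through symptoms". H2 likewise speaks of improvement in symptoms, and its controls are given as "controlling for change in glucose tolerance and inflammation (week 8) and for baseline levels of diurnal amplitude, symptoms, glucose tolerance, and inflammation". Change in the other symptom is not among them. The confounder screen in the analysis section would not add it either: it looks for variables correlated with both adherence and the dependent variables, and the symptoms are themselves dependent variables.

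The sample-size text reads: "We have planned analyses based on availability of data from 125 participants, allowing for attrition of 25 participants". It gives power of .81 for one indirect effect of amplitude change on QoL through symptom change, at f2 = .25 (amplitude to symptoms and QoL) and f2 = .40 (symptoms to QoL). It does not mention that there are two models.

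**The concern.** There are two separate problems.

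**Decision rule.** H2 and H3 are worded once and tested twice. If a positive result in either model may be reported as support, each hypothesis has two chances at .05. If both are required, the error is controlled, but the power statement for a single indirect effect does not describe the power to succeed in both.

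**Attribution.** Each SEM holds one symptom. If changes in mania and depression are correlated, the mania-to-QoL coefficient picks up whatever depression contributes to QoL, and the reverse. The stated aim is mechanism, so an indirect effect credited to the wrong symptom would be a substantive error in the main result.

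The adherence-to-amplitude path (H1) appears in both models. That adds no error, but one test would be reported twice.

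**Working it through.** **Inputs from the protocol article.** Alpha .05 two-sided; two core models; N = 125; f2 = .25 and .40. As partial correlations, r = √(f2/(1+f2)):
- √(.25/1.25) = .447
- √(.40/1.40) = .535

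**Assumed, because the article gives no figure.** The mania-depression correlation, varied from 0 to .5.

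**1. The plan's own power figure.** Noncentral F with λ = f2 × N gives λ = 31.25 and 50. Path powers are .9998 and above .9999, so joint-significance power is .9998; a Sobel test gives .99. The stated .81 is not reproduced. Reading .25 and .40 as f gives .787, and reading them as correlations gives .796. Power at any adjusted level therefore cannot be quoted until these inputs are settled.

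**2. Error if either model may count.**
- Independent tests: 1 − .95² = .0975
- Correlated tests: .095 at correlation .3, .0905 at .5, .083 at .7

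For H2, which is a single path, this applies whenever amplitude is unrelated to both symptoms. For the indirect effect, a false positive needs both links to be significant, so the rate depends on which link is null. In simulation (N = 125, joint-significance test, observed variables in place of the latent amplitude), at least one model was significant:
- in 9.7% to 10.2% of runs when amplitude does not affect symptoms but symptoms affect QoL;
- in 0.4% to 0.7% of runs when every path is null.

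If both models must succeed, there is no inflation.

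**3. False mania-to-QoL path.** Let QoL depend only on depression, at .535. The mania-QoL correlation is then .535 × ρ, where ρ is the mania-depression correlation. Fisher-z power is Φ(atanh(.535ρ) × √122 − 1.96):

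| ρ | .535ρ | z | Fisher-z power | Simulated (4,000 runs) |
|---|---|---|---|---|
| .2 | .107 | 1.19 | .22 | 22% |
| .3 | .160 | 1.79 | .43 | 44% |
| .4 | .214 | 2.40 | .67 | 67% |

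A joint model holds this at 5%.

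**4. False mania indirect effect (amplitude to mania to QoL).** QoL again depends only on depression, with the stated effect sizes, N = 125 and 4,000 runs per setting:

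| What is true | Mania model alone | Depression also in the model |
|---|---|---|
| Amplitude affects both; residual correlation 0 / .2 / .3 / .5 | 5% / 19% / 39% / 79% | about 5% |
| Amplitude affects depression, and mania follows depression; link 0 / .2 / .3 / .5 | 0.2% / 3% / 10% / 50% | about 4% or less |
| Amplitude affects depression only; residuals correlated .3 to .5 | 2% to 5% | about 5% or less |

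H3 starts one link earlier, at adherence. Under a joint-significance test that link must be significant too, so it cannot raise these rates.

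**The case against.** The strongest reply is that the article states no either-model rule. Its lead-in to the hypotheses names mania and depression together, which fits a prediction about both at least as well as a prediction about either. If both are required, or if each symptom is reported as its own hypothesis, 5% holds. The article is also condensed, describes a single-arm mechanistic study, refers to a separate statistical analysis plan and commits to ICH E9, so a multiplicity rule may exist elsewhere. This stands: the inflation is conditional. What remains is that the article fixes a flat .05 and two separate models without saying how they combine.

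A second reply is that the joint model answers a different question. Separate models give each symptom's unadjusted association. A joint model gives its effect with the other held fixed, and where one symptom drives the other, adjustment removes part of a real pathway. That is fair, and it is a reason to keep the separate models as supportive analyses. It does not help a mechanistic conclusion that rests on the separate models alone.

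Third, people in a current mood episode are excluded at entry and no mania-depression correlation is given, so the correlations used here are assumptions. That also stands.

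Three stronger readings are tempting but not supported:
- **Three primary outcomes mean three tests.** That would give 1 − .95³ = 14.3%, but QoL is the end point inside both SEMs and not a third parallel test.
- **The 22%, 44% and 67% are false indirect effects.** They describe the mania-to-QoL path only. The indirect effect also needs amplitude to be related to mania.
- **Adjusting alpha must cost material power.** At the printed f2 values it does not (see the change proposed below).

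**Conclusion.** The point holds in a limited form, in two parts.

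The error for H2 or H3 reaches about 9% to 9.75% if either model may support the hypothesis. For H3 this arises only when amplitude does not affect symptoms but symptoms affect QoL; the rate is under 1% when all paths are null. A reader might infer that the 5% level simply fails. The article does not support that, because it states no success rule.

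The attribution problem does not depend on the success rule. As specified, the mania model cannot tell a mania path from a depression path. The false indirect effect is about 19%, 39% and 79% at residual correlations of .2, .3 and .5 if amplitude affects both symptoms. It is at most about 5% if amplitude affects depression only and the residuals are merely correlated. These figures rest on assumed correlations, the printed f2 values, QoL driven by depression alone, and observed variables standing in for the latent amplitude.

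**What to change.** Fit one SEM with MADRS and YMRS as parallel, correlated mediators between clock gene amplitude and QoL. H1 is then estimated once, and each indirect effect is adjusted for the other symptom. Keep the two separate models as supportive analyses.

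State whether H2 and H3 require one symptom or both. If either suffices, test the two H2 paths and the two H3 indirect effects with Holm, or in a fixed order with one symptom named first.

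Restate power for the chosen rule and correct its inputs, since .81 is for a single indirect effect and does not follow from the printed f2 values. At those values, joint power is .9998 at .05 and .9995 at .025, so the adjustment costs almost nothing. If .25 and .40 were meant as f, it falls from about .79 to about .69.

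No new data or visits are needed. The costs are a few more parameters at N = 125 and a changed meaning for each symptom path, which becomes an effect with the other symptom held fixed.

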**Methods:**

One-hundred fifty participants diagnosed with BD 1 or II will be recruited via advertising in the local community. Main inclusion criteria include: obtaining medical treatment for BD; current sleep or circadian problems; self-reported eating period of ≥ 12 h; no eating disorder or other health conditions that would hinder or limit the safety of following TRE; and not currently experiencing a mood episode, acute suicidality, psychosis, alcohol or substance use disorder. Participants will be asked to complete a baseline period in which daily food intake is logged online for two weeks. After baseline, participants will be asked to follow TRE for 8 weeks and to continue to complete daily food logging during this time. Symptom severity interviews will be conducted by phone or videoconference at baseline, mid-intervention (6 weeks post-baseline), end of intervention (10 weeks post-baseline), and 6 months post-baseline. Self-rated symptom severity and quality of life data will be gathered online at the same time points as symptom severity interviews, and at 16 weeks post-baseline (6 weeks after the TRE period ends). To assess potential mechanisms of change, we will examine the change in diurnal amplitude of ‘clock’ gene expression as a primary mediator at 8 weeks compared to baseline. We will further test whether diurnal amplitude of clock gene expression is predictive above and beyond the role of two covariate potential mediators, glucose tolerance and inflammation at 8 weeks relative to baseline. To provide an index of whether TRE successfully decreases emotional lability, participants will be asked to complete 5 mood assessments per day for 7 days at baseline and at 10 weeks. These mood assessments will be optional.

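### The stated power of .81 for the amplitude–symptoms–QoL indirect effect does not follow from the stated effect sizes, which give about .99 or more at N = 125

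*Protocol article*

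**What the plan says.** The Statistical analysis plan section of the protocol article fixes the inputs. On sample size: "We have planned analyses based on availability of data from 125 participants, allowing for attrition of 25 participants". On the test level: "Analyses will be conducted using two-tailed tests with alpha set to .05". On adjustment: "Power analyses were based on inclusion of two covariates". On the first effect: "We assume moderate effects for diurnal amplitude on symptoms and QoL (f2 = .25"), followed by the remark that smaller effects would not fit circadian rhythm theory. The symptoms-to-QoL effect is set at f2 = .40.

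The output is that "power to detect the indirect effect of change in amplitude of gene expression on QoL via symptom change is .81". A separate figure above .90 is given for the full model by RMSEA.

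The core structural equation model starts one step earlier, at TRE adherence. Under Hypotheses, H1 has adherence predicting change in amplitude, and H3 reads "There will be an indirect effect of TRE adherence on QoL through symptoms". No effect size is given for any path from adherence.

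**The concern.** An f2 of .25 means that the predictor accounts for .25/1.25 = 20% of the variance not explained by the other terms. With 125 participants, a single path of that size is detected almost with certainty, and the symptoms-to-QoL path is larger still. A joint power of only .81 looks too low for these inputs.

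The stake is interpretation, not sample size. The section treats effects below f2 = .25 as contrary to the theory under test, so a null result would be read against that benchmark. If .81 was in fact computed for a much smaller effect, the benchmark is mislabelled. If f2 = .25 is right, the trial has far more power at that effect than the text claims. A reader cannot tell which effect the trial could exclude.

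**Working it through.** **Inputs** (all from the Statistical analysis plan section): N = 125; two-sided alpha .05; two covariates; f2 = .25 (path a, amplitude to symptoms); f2 = .40 (path b, symptoms to QoL). Path a has 3 predictors (residual df 125 − 3 − 1 = 121). Path b has 4 (residual df 120).

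**Attempt to reproduce .81, joint significance.** Each path is a 1-df F test with noncentrality λ = f2 × N. The power for the indirect effect is the product of the two path powers.
- Path a: λ = .25 × 125 = 31.25, power .9998.
- Path b: λ = .40 × 125 = 50, power > .9999.
- Joint power: .9998.

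**Sobel approximation**, which is more conservative. z = 1/√(1/z_a² + 1/z_b²), with z_path² = f2 × residual df.
- z_a² = .25 × 121 = 30.25; z_b² = .40 × 120 = 48.
- z = 1/√(1/30.25 + 1/48) = 4.31.
- Power = Φ(4.31 − 1.96) = .991.

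**Simulation** with two covariates gives .999, with or without a direct amplitude-to-QoL path of f2 = .25.

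So .81 is not reproduced. With these f2 values it would be reached at about 38 participants (joint significance) or 57 (Sobel).

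**Could another choice explain it with f2 unchanged?**

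| Variation | Joint | Sobel |
|---|---|---|
| N = 100 | .999 | .970 |
| 9 predictors in the first equation, N = 125 | .9998 | .987 |
| alpha = .001, N = 125 (5 predictors) | .985 | .837 |

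None of these gives .81, and the last is far from the stated alpha. Random error in the amplitude measure lowers power in simulation to .99 at reliability .7, to .94–.95 at .5, and to .77–.80 at .3. Only a very low reliability comes close, and the text states none.

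**Could another metric explain it?** At N = 125, two covariates, joint significance:
- *.25 and .40 as standardised paths.* f2 = .0625/.9375 = .067 and .16/.84 = .190; λ = 8.33 and 23.81; power .817 × .998 = **.815** (.79 by simulation).
- *.25 and .40 as Cohen's f.* f2 = .0625 and .16; λ = 7.81 and 20; power .792 × .993 = **.787** (.76 by simulation).

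The standardised-path match holds for joint significance only; Sobel with the same paths gives .685. Working backwards, the f2 on the limiting path that yields .81 at N = 125 is about .065.

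**The case against.** The strongest reply is that the model uses a latent amplitude variable measured by three genes, that its loadings and reliability are not printed, and that the cited power methods cannot be seen here. A correct calculation with poor measurement could give .81 from f2 = .25 and .40. This stands as far as the cause goes: a mislabelled metric is the closest match but is not proven. It does not rescue the text, because the reliability needed is about .3 and no such assumption is stated. It is also fair that, if the f2 values are right, .81 errs in the conservative direction and nothing in the design has to change.

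Several stronger readings are tempting but not supported:
- *That power for H1 and H3 is lower than stated.* No power is stated for them; the section labels its figure as running from amplitude. H3 as worded runs through symptoms only, so it is not the full chain through amplitude. Any power for adherence paths would need an assumed effect.
- *That planning for two covariates contradicts H2*, which adjusts by "controlling for change in glucose tolerance and inflammation (week 8) and for baseline levels of diurnal amplitude, symptoms, glucose tolerance, and inflammation". The two covariates are described as possible confounders of adherence and outcome, and may be additional to H2's own controls.
- *That the RMSEA figure above .90 is unattainable.* The bare chain has few degrees of freedom, but the planned model also includes covariates, which can add to them. The text does not allow a contradiction to be shown.

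**Conclusion.** The concern holds for the indirect-effect power. On the printed inputs, power is about .99 (Sobel) to over .999 (joint significance), not .81. This assumes that f2 is the usual partial effect size for each path and that amplitude is measured with reasonable reliability (.99 still holds at .7).

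Which element is wrong cannot be determined from the document. If .25 and .40 are standardised paths, .81 is about right, but the effect powered for explains roughly 6% of variance (.25² = .0625) instead of 20%. If f2 is right, the power is understated.

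The .81 also applies only to the amplitude–symptoms–QoL segment. It says nothing about the paths from adherence in H1 and H3. That is a limit on the figure's scope which the text should make plain, not evidence that those hypotheses are underpowered.

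**What to change.** Keep N. Re-run the calculation and then do one of the following:
- relabel the effect sizes in the metric actually used (if standardised paths, .25 and .40, with f2 about .067 and .19);
- if f2 is correct and measurement error was modelled, state the reliability or loadings assumed;
- if f2 is correct and no such assumption was made, restate the power as about .99.

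Name the method (joint significance, Sobel or simulation). Then align the remark that smaller effects do not fit the theory with the effect size actually powered for. Add one sentence saying that the figure covers amplitude to symptoms to QoL and not the paths from adherence in H1 and H3, for which no effect size is given.

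The cost is one rerun and a few reworded sentences. No hypothesis, test, alpha level or participant number changes.

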#### Secondary analyses

Within analyses for H4, the potential moderation effects of age of onset, we will consider the effects of age of onset as an interaction term with TRE adherence in the above-described SEM models. For TRE-related changes in secondary outcomes, we will use SEM models paralleling those used for primary hypotheses to determine TRE changes in sleep (actigraphy), emotional variability (assessed by EMA) at 8 weeks compared to baseline.

## Discussion

This study will provide novel evidence about the mechanisms of change for TRE in BD. Previous work suggests that TRE has potent influences on circadian function, allowing a test of whether changes in the diurnal amplitude of clock gene expression help predict improvements in symptoms and downstream QoL. Although we focus on strong hypotheses regarding diurnal amplitude of clock gene expression, we will gather a rich dataset of diurnal parameters, which will allow exploratory analyses of which aspects of diurnal function are most clearly changed by TRE, and which of those changes are most critically relevant for symptom improvement. At the same time, we will consider the extent to which TRE changes other key biological parameters associated with BD outcomes—namely, pro-inflammatory cytokines as markers of inflammation. Taken together, we will assess the benefits of TRE for three critically important processes tied to BD.

Understanding more about the mechanisms of change could help consider a broader array of medical as well as psychiatric outcomes that would be suitable targets of TRE. Given the high prevalence of comorbid medical conditions and their prospective links to poorer psychiatric outcomes, enriching the toolkit for addressing these key biological processes is an important goal. The rich information about possible mechanisms will also help refine understanding of which individuals might be most likely to benefit from TRE. Assessing a range of outcomes and mechanisms related to TRE in BD has important public health implications, as TRE can be easily disseminated worldwide using online technologies.

Despite the novel strengths of the current study, there are important limitations to acknowledge. Although we are building on intervention tools that have been used successfully in medical populations, it is possible that more intensive support and coaching will be needed for those with BD to successfully implement these lifestyle changes. Hence, future research may need to refine how TRE is provided for those with BD. Second, there are significant weaknesses in our assessments of diurnal function. Although we have taken a multi-modal, rich approach to assessing many diurnal parameters, true circadian functions cannot be effectively assessed without a constant routine paradigm [132]. We see the current study as a first step toward the goal of understanding which expressions of circadian function might be shifted with TRE, thereby opening the door for more careful mechanistic work in future studies.

